### Data management and monitoring

Our IRB-approved protocol specifies plans for data entry, coding, security, and storage of data on a secure server. Our web-based assessment system includes many mechanisms to protect data integrity and promote data quality (e.g., only allowing valid values, warnings of missing responses), and the data manager will maintain detailed data management procedures (e.g., range checks, data quality reports). The Principal Investigator will meet weekly with study personnel to discuss study goals, participant recruitment/retention, progress in data collection and analysis, and any adverse events or participant complaints.

The study team has established procedures for monitoring and managing risks to participants. A Data and Safety Monitoring Board of five external professionals with varied clinical and research expertise will review study reports and summaries of human subjects’ issues annually and submit recommendations regarding study continuation or proposed modifications. Study modifications will be approved by the IRB, and any significant changes in methods will be reported to the project’s program officer and described in an update to the registered protocol on https://ClinicalTrials.gov. The Principal Investigator and approved study team members will have access to the final trial datasets. Study co-investigators and consultants can access the datasets by request after obtaining IRB approval. Per NIMH policy, a deidentified dataset will be prepared for the National Data Archive.

### Statistical analyses

#### Aim 1

Our primary analytical tool for Aim 1 will be a two-way analysis of variance with interaction using mixed-effects linear models for continuous outcomes and generalized linear mixed models for categorical variables. We will use an intent-to-treat approach. We will examine patterns of missingness and, if necessary, use imputation methods using available covariates [141, 142]. For exploratory analyses, we will use variable selection methods such as Lasso and elastic net to get parsimonious models that fit well. Analyses will be conducted at the end of the trial; no interim analyses are planned.

For implementation outcomes, we hypothesize that relative to REP only, TEAM, LEAD, and their interaction will significantly improve (1) the number of DOCC service encounters per case and (2) collaborative care competencies within the practice. We will test effects on outcomes at months 6, 12, 18, and 24. Fixed effects include time, condition, and practice, and random effects will account for nesting. We will conduct planned contrasts to test differences between conditions.

For patient outcomes, we hypothesize that relative to REP only, TEAM, LEAD, and their interaction will significantly improve (1) child symptom severity and (2) quality of life. Fixed effects include time and condition, and random effects will account for nesting. As exploratory analyses, we will run larger models adjusting for demographic and baseline clinical variables and assess goodness of fit.

#### Aim 2

We hypothesize that TEAM practices will show significant gains in our proposed TEAM targets (team functioning, integration/quality) and that LEAD practices will show significant gains in our proposed LEAD targets (implementation leadership, implementation climate). We will use larger models to adjust for demographic and baseline clinical variables, test goodness of fit, and compare different time periods to check model fit. We will test if the association between each condition (TEAM, LEAD) and each implementation outcome is mediated by their respective targets and explore serial mediation.

#### Aim 3

We will test moderation of TEAM effects by provider characteristics, moderation of LEAD effects by practice characteristics, and moderation of TEAM and/or LEAD effects on child outcomes by family characteristics. We will adapt standard tests for interaction for a detailed study of the candidate moderators. We will use Wallace et al.’s method to derive a single optimal linear combination of moderators [143]. The composite moderator typically has a larger *ES* than any one variable; the relative weights of the composite index can be interpreted to determine the relative importance of moderators for practical applications.

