#### Aim 1: test the effects of TEAM and LEAD on implementation outcomes and child clinical outcomes

Our implementation outcomes are DOCC service delivery, specifically the number of encounters for each case (primary), and change in practice-level care management competencies (exploratory) at 4 timepoints (6, 12, 18, and 24 months). We will also examine secondary clinical outcomes (change in severity of child symptoms). We hypothesize that augmenting REP with TEAM alone or LEAD alone is superior to Standard REP, and that TEAM + LEAD is superior to all other conditions because it targets both levels.

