#### Professional and caregiver assessments

Practice staff will complete assessments at 0, 6, 12, 18, and 24 months. Caregivers will complete assessments at 0, 3, 6, and 12 months and provide consent for their child’s teacher to complete rating scales at each timepoint. Measures are listed in Table 2. All assessments can be completed online, on paper, or by phone with research staff. Participants will be paid for each completed assessment. We estimate high retention rates for practice staff (> 90%) and caregivers (> 85%) based on our previous trials (91–92%) [107–109]. We will use strategies from prior trials (e.g., trained staff, on-time bonus payments) to support retention.

**Table 2 Tab2:** Primary assessment constructs, measures, sources, and timepoints by study aim

Construct	Measure	Source	Month					
			0	3	6	12	18	24

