##### Mental Health Practice Readiness Inventory (MHPRI)

The MHPRI [119] will document practice-level care management competencies shown to predict care uptake [120, 121].

Practice staff will rate each of the 32 items at the practice-level (0 = no function exists; 1 = some function; 2 = function is complete). We will aggregate all informants’ scores to create a total score for practice achievement of care management competencies.

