### Power and sample size

Our power calculations for Aim 1 are based on comparisons of provider and patient outcomes among the six practices in each of the four conditions in the factorial design. For our primary implementation outcome (number of DOCC sessions), we estimate 80% power to detect an effect size (ES) of 0.42. Given our modest practice sample size, we will explore group differences in practice-level CCM core competencies. In our prior trial, large ESs were found for provider changes in behavior management practices (*ES* = 0.78) and perceived competencies (*ES* = 0.77) [107]. For patient outcomes, we assume an ICC of 0.01 in cases treated by the same provider and 20% attrition based on prior work [107, 109]. In a simple RCT with 262 cases/condition, we can detect an effect size as small as 0.25. The effect size for clinical improvement in individualized targets in our prior trial was 0.60, indicating that our sample size provides adequate power to detect group differences in patient outcomes [107].

Power calculations for mediator analyses (Aim 2) are based on simulation studies [140]. Because the sample sizes per cell are modest (6 sites per condition), we are powered to detect large effects. This seems justifiable insofar as smaller effect sizes (e.g., 0.35–0.50) are of less interest given the higher cost of using more intensive combined implementation strategies. Thus, our mediational tests are powered only for a large effect size. For our moderator analyses (Aim 3), we have power 0.80 to detect small effects of *f-square* = 0.03.

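### No stated Aim 1 or Aim 2 model adjusts the staff-rated practice outcomes (MHPRI, PCTDS, ILS, ICS) for their own month-0 score, and the change comparison the article points to is less precise

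*Protocol article*

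**What the plan says.** The assessment schedule gives five staff waves: "Practice staff will complete assessments at 0, 6, 12, 18, and 24 months". Table 2 shows the MHPRI, PCTDS, ICS and ILS at all five. The MHPRI is reduced to one value per practice: "We will aggregate all informants’ scores to create a total score for practice achievement of care management competencies".

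The Study aims section defines the competencies outcome as "change in practice-level care management competencies (exploratory) at 4 timepoints (6, 12, 18, and 24 months". In Statistical analyses, Aim 1, the implementation paragraph says "We will test effects on outcomes at months 6, 12, 18, and 24" and then "Fixed effects include time, condition, and practice, and random effects will account for nesting".

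Aim 2 is worded as gains. For example, it expects that "LEAD practices will show significant gains in our proposed LEAD targets (implementation leadership, implementation climate". Its only named adjustment is "We will use larger models to adjust for demographic and baseline clinical variables".

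Baseline ILS and ICS are used elsewhere, as moderators of LEAD (Measures, Practice level; Aim 3). Neither the MHPRI nor the PCTDS is named as a baseline term in any model.

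**The concern.** These outcomes are compared across 24 practices: 12 v 12 for each factorial main effect and 6 v 6 for a contrast between two conditions. At that size chance differences at month 0 are large, and the month-0 score of the same measure is usually the strongest predictor of the later score. The article collects that score, but the two models that would benefit most do not name it. The Aim 2 adjustment set, demographic and baseline clinical variables, does not name the starting level of a staff-rated team or organizational target.

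The article concedes that competencies will only be explored because there are few practices, and that mediation is powered only for large effects. The effect of condition on its target is the first leg of each mediation test, so precision lost there also weakens the mechanism question, which is a stated purpose of the trial.

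**Working it through.** **No figure to reproduce.** The article gives no power or detectable difference for the MHPRI, and for mediation only that large effects are targeted. Its 80% power at an effect size of 0.42 is for the number of DOCC sessions, which has no baseline, so it does not bear on this point.

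**Inputs from the article**
- Six practices per condition (Power and sample size: "comparisons of provider and patient outcomes among the six practices in each of the four conditions in the factorial design"), so n = 12 per level of each factor.
- An effect size of 0.78, the prior-trial figure for provider changes in behavior management practices. It is borrowed as an illustration and treated as practice-level SD units.

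**Assumptions**
- Two-sided alpha of 0.05.
- Equal variance (set to 1) at month 0 and follow-up.
- Baseline-to-follow-up correlation rho between 0.3 and 0.9; the article gives none.

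**Formulas, one follow-up wave, per-practice residual variance V**
- Follow-up only: V = 1
- Change score: V = 2(1 − rho)
- Baseline-adjusted: V = 1 − rho²

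Standard error = sqrt(2V/12). Power comes from the noncentral t with noncentrality 0.78/SE and 20 df, or 19 df with the covariate. For example, at rho 0.5 the change score has V = 1.00, SE = 0.408 and noncentrality 1.91, giving 44%. The adjusted analysis has V = 0.75, SE = 0.354 and noncentrality 2.21, giving 55%.

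| rho | V change | V adjusted | Power, follow-up only | Power, change | Power, adjusted |
|---|---|---|---|---|---|
| 0.3 | 1.40 | 0.91 | 44% | 34% | 48% |
| 0.5 | 1.00 | 0.75 | 44% | 44% | 55% |
| 0.7 | 0.60 | 0.51 | 44% | 65% | 72% |
| 0.8 | 0.40 | 0.36 | 44% | 82% | 86% |
| 0.9 | 0.20 | 0.19 | 44% | 98% | 99% |

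Against the change score, adjustment cuts the variance by the fraction (1 − rho)/2: 35%, 25%, 15%, 10% and 5% down the table. Unrounded, the power gain is 3.6 points at rho 0.8 and 0.4 points at rho 0.9. The difference detectable with 80% power, change v adjusted, is 1.42 v 1.15, 1.20 v 1.04, 0.93 v 0.86 and 0.76 v 0.72 SD at rho 0.3, 0.5, 0.7 and 0.8.

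**Chance imbalance.** The SD of the month-0 difference is sqrt(2/12) = 0.41 for 12 v 12 and sqrt(2/6) = 0.58 for 6 v 6. The probability that it exceeds 0.5 SD in either direction is 22% and 39%. Given an observed month-0 difference d, a change comparison is expected to be off by (rho − 1)d, opposite in sign to d. At rho 0.5 and d = 0.41 that is −0.5 × 0.41 = −0.20 SD. Averaged over randomizations the error is zero.

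**Does the month-0 score fit the stated model?** With 24 practices and four follow-ups, fixed practice and time terms give a design matrix of rank 27. Adding the month-0 practice score leaves the rank at 27, and so does adding condition. Both are constant within a practice, so fixed practice terms absorb them. If month 0 is instead a response with condition-by-time terms, the design has rank 40 for 40 columns and is estimable. That is a change-from-baseline analysis, but the article names no condition-by-time term.

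**The case against.** The strongest objection is that the point rests on silence. The article is condensed, it refers to a separate IRB-approved protocol, its list of fixed effects is not worded as closed, and baseline covariates are often left to the analysis plan. Its Lasso and elastic net selection for exploratory analyses could also bring the month-0 MHPRI in. This stands as a limit on confidence. It does not remove the point, because the article does name its fixed effects and the Aim 2 adjusters, and its wording points to a less efficient estimator.

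Three stronger readings are tempting, and the article does not support them.
- A reader might infer that the month-0 scores are used in no model. Baseline ILS and ICS do enter the Aim 3 models as moderators of LEAD.
- A reader might infer that raw baseline imbalance passes straight into the comparisons. That would need a follow-up-only analysis, whereas the outcomes are framed as change and gains. The baseline is then subtracted, and the remaining problem is over-correction and lower precision. It is not bias under randomization and not an inflated type I error.
- A reader might infer that the loss is always substantial. It becomes small at high correlations, and averaging several raters per practice makes higher correlations plausible.

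It is also fair to object that 0.78 is a provider-level figure for a different measure. It is used here only to put the variance ratios on a power scale.

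**Conclusion.** The point holds as a matter of precision for the exploratory MHPRI and the Aim 2 targets PCTDS, ILS and ICS. Baseline adjustment has more power than a change comparison at every correlation examined, from 14 points at rho 0.3 (34 v 48%) down to under half a point at rho 0.9. These figures assume one follow-up wave, 12 v 12 practices, equal variances and an effect of 0.78 practice-level SD; the correlation itself is unknown.

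The primary outcome is unaffected, and no primary conclusion depends on this. It is still worth settling before analysis, because the data are already planned and there are few practices.

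**What to change.** In Statistical analyses, Aim 1, state that the MHPRI at months 6 to 24 is modelled with the practice's month-0 MHPRI score as a covariate, and that practice is a random rather than a fixed effect. The second change is needed for the first to work, since fixed practice terms absorb both the month-0 score and condition. In Aim 2, make the same statement for PCTDS, ILS and ICS: each target-engagement and mediator model adjusts for the month-0 value of that same target.

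An equivalent alternative is a longitudinal model with month 0 as one of the outcomes, condition-by-time terms, and condition means constrained equal at month 0.

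The cost is a change of wording and, with the covariate, about one practice-level residual degree of freedom (20 to 19), which the power figures already include. No new data are needed.

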## Methods

### Study design

We propose a hybrid type 3, cluster-randomized effectiveness–implementation trial in a 2 × 2 factorial design in 24 pediatric primary care practices across Pennsylvania. After all sites receive Standard REP, they will be randomized to one of four conditions: (1) Standard REP only (continued technical assistance), (2) TEAM, (3) LEAD, or (4) TEAM + LEAD. Figure 1 outlines the trial design. Care teams will deliver DOCC to 25 children with elevated behavioral problems and their caregivers. We will collect longitudinal data from practice staff and caregivers. SPIRIT, CONSORT, and TIDieR checklists [113–115] are in Supplemental File 1, and CONSORT flow diagrams are in Supplemental File 2. All procedures were approved by the University of Pittsburgh Institutional Review Board.

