### Setting and participants

#### Practices

Study sites will be 24 primary care practices affiliated with the Pennsylvania Chapter of the American Academy of Pediatrics Medical Home Program (PA-MHP) [4, 7, 116]. These practices are heterogenous with respect to their size, location, health system, insurance mix, and population diversity. PA-MHP leadership identified eligible and interested practices and organized orientation meetings with key practice leaders.

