#### Caregivers

We will enroll up to 25 caregivers of 5–12-year-old children in each practice for a possible total of 600 caregivers. Eligibility criteria are (1) child age (5–12 years), (2) parent/guardian with parental rights, and (3) child meets clinical cutoff on 7-item externalizing problems scale of the Pediatric Symptom Checklist-17 (PSC-17) [117]. Based on prior trials, we expect to recruit more female than male caregivers and for participants to vary in race/ethnicity by practice. Our primary informant is the caregiver due to the children’s young age and ethical concerns about assessing children without face-to-face contact.

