#### Implementation outcomes

##### Services Provided Log (SPL)

After each service encounter, providers will record the type of contact (e.g., treatment session, collaborative care meeting), individuals present, intervention content, and plans for next contact [107, 108]. Our primary outcome is the number of DOCC service encounters delivered to each patient by all providers.

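### Practice is listed as a fixed effect beside condition in the implementation-outcome model, so the TEAM, LEAD and TEAM×LEAD main effects on the primary outcome cannot be estimated as specified

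*Protocol article*

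**What the plan says.** Under Study design, the Protocol article makes the practice the unit of allocation: "After all sites receive Standard REP, they will be randomized to one of four conditions". Under Practices, "Study sites will be 24 primary care practices", and the Power and sample size section works with comparisons "among the six practices in each of the four conditions in the factorial design". Under Caregivers, enrolment is capped at 25 "in each practice for a possible total of 600 caregivers".

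The Services Provided Log section defines the primary endpoint: "Our primary outcome is the number of DOCC service encounters delivered to each patient by all providers".

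Under Statistical analyses, Aim 1 is to be analysed as a two-factor layout with interaction, using mixed models. The paragraph on implementation outcomes specifies "Fixed effects include time, condition, and practice, and random effects will account for nesting" and then announces contrasts between the conditions. The next paragraph, on patient outcomes, specifies "Fixed effects include time and condition, and random effects will account for nesting". The two sentences differ only in the word practice. Nowhere does the article describe practice in the first model as a random factor or as shorthand for practice-level covariates.

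**The concern.** A fixed effect for each practice absorbs every difference between practices. In a cluster-randomized trial, the effect of the randomized strategy is itself a difference between practices. Once the 24 practice levels are in the fixed part of the model, nothing is left from which to estimate TEAM, LEAD or their interaction.

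This is the stated model for the primary outcome. An analyst who follows it literally will see condition dropped, or will get a contrast between whichever practices the software takes as reference levels. If practice is instead coded as fixed within condition, condition means can be contrasted, but against the variation among children within a practice. That treats up to 600 children, not 24 practices, as the randomized units.

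**Working it through.** **The article's own figure.** The only number given for the primary outcome is an effect size of 0.42 at 80% power. No ICC, significance level or comparison is stated with it, so it cannot be reproduced. Assuming two-sided 5%, the detectable effect is (1.96 + 0.842) × √(2 × DE / n), with DE = 1 + (m − 1) × ICC:
- 12 v 12 practices, m = 25 (n = 300), ICC 0.10: DE = 3.4, effect 0.422.
- 6 v 6 practices, m = 25 (n = 150), ICC 0.03: DE = 1.72, effect 0.424.
- ICC 0.01, which the article states only for patient outcomes among cases of the same provider: 0.255 and 0.360.

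The 0.42 is therefore neither confirmed nor refuted, and nothing below depends on it.

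**Step 1: estimability, encounters per case.** Inputs: 24 practices, 6 per condition, 25 cases each, so 600 rows.
- Intercept plus 24 practice indicators: rank 24.
- Adding TEAM, LEAD and TEAM×LEAD: 28 columns, rank still 24.
- A trial least-squares fit on simulated data showed no change in residual sum of squares when condition was added to practice (difference about 10⁻¹³), with 600 − 24 = 576 residual degrees of freedom either way.

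The three condition degrees of freedom lie wholly inside the 23 between-practice contrasts. This needs no assumed ICC and holds for any number of cases per practice.

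**Step 2: estimability, repeated practice-level score.** Inputs: 24 practices at months 6, 12, 18 and 24, so 96 rows.
- Intercept, time and practice: 1 + 3 + 23 = rank 27.
- Adding condition: rank 27.
- Adding condition-by-time: 3 × 3 = 9 further columns, rank 36.

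The condition main effect is again aliased, but condition-by-time is estimable.

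**Step 3: size of the error if a contrast is forced out.** Suppose condition means are compared using within-practice error. With total variance 1, the true variance of a practice mean is ICC + (1 − ICC)/m, whereas the test uses (1 − ICC)/m. The ratio is R = (m × ICC + 1 − ICC)/(1 − ICC), and the true type I error at nominal 5% is 2 × [1 − Φ(1.96/√R)].

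| Assumed ICC | R, m = 25 | Type I error, m = 25 | R, m = 20 | Type I error, m = 20 |
|---|---|---|---|---|
| 0.01 | 1.24/0.99 = 1.253 | 0.080 | 1.19/0.99 = 1.202 | 0.074 |
| 0.05 | 2.20/0.95 = 2.316 | 0.198 | 1.95/0.95 = 2.053 | 0.171 |
| 0.10 | 3.40/0.90 = 3.778 | 0.313 | 2.90/0.90 = 3.222 | 0.275 |

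A simulation of 40,000 trials per setting, with normally distributed outcomes, gave 0.081, 0.196 and 0.316 for m = 25, and 0.074, 0.170 and 0.278 for m = 20. Contrasting two arbitrary reference practices gave nearly the same (0.081, 0.196 and 0.312 for m = 25). A practice-level test on 24 − 4 = 20 degrees of freedom stayed between 0.049 and 0.052 throughout.

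**The case against.** The best defence is that the word practice is a slip made in condensing the plan. The same sentence goes on to say that random effects will handle nesting, and the parallel patient-outcome sentence omits practice. That is plausible, but it does not make the sentence right. Once practice is fixed, no between-practice variation remains for a random effect to describe. The article also never names practice as random. Nor is this a detail left to an analysis plan: the article states a specification, and that specification does not work.

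Three other points on this side stand, and they set the limits of the finding.

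First, a reader might infer that Aim 1 as a whole has no answer. The documents do not support that. Aim 1 also covers clinical outcomes, and their model lists only time and condition as fixed.

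Second, a reader might infer that the competency outcome is lost too. It is a practice score repeated over time and analysed for change, so condition-by-time remains estimable. That term is not among the fixed effects named, but the list is introduced as what the model includes and also leaves out the interaction that the article plainly plans, so it need not be exhaustive.

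Third, a reader might infer that the trial will produce many false positives. That requires a particular coding, which the article does not state, and a practice-level ICC for encounters, which it does not give. Full aliasing usually shows up at model fitting, which lowers the chance of a silent error. At an ICC of 0.01 the excess is modest, and cases per practice are capped at 25, not fixed at 25.

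**Conclusion.** The point holds for the condition main effects in the implementation-outcome model. As written, TEAM, LEAD and TEAM×LEAD are completely aliased with practice, so the planned condition contrasts for encounters per case cannot be estimated. This follows from the allocation alone and rests on no assumed figure.

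The false-positive rates are conditional. They apply only if a contrast is forced out against within-practice error, and they rest on assumed ICCs, equal cases per practice and normal theory, which has not been shown to carry over to an encounter count. On those terms, true type I error runs from about 8% to 31% with 25 cases per practice, and from about 7% to 28% with 20, over ICCs of 0.01 to 0.10. Neither a failure of Aim 1 as a whole nor a certain inflation of false positives follows from the text.

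**What to change.** In the implementation-outcome paragraph, delete practice from the list of fixed effects and name it as a random intercept, which the wording of the clinical-outcome model already allows. State that TEAM, LEAD and TEAM×LEAD are tested on between-practice degrees of freedom with a small-sample correction (for example Kenward–Roger in a linear mixed model, or an equivalent for a count model). At most about 20 are available (24 practices minus four cells). Adjusting for the three cohorts would take two, leaving 18, and a Medicaid-rate stratum would take more. If change in the competency score is to be judged by condition-by-time, list that term.

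The cost is one or two sentences, with no change to data collection. Whether 0.42 is the right detectable effect under this model is a separate matter that the stated inputs cannot settle.

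### Aim 1 hypothesises that TEAM + LEAD beats every other condition, but the analysis section restates this as an interaction, which tests additivity; the matching contrasts are not stated for patient outcomes

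*Protocol article*

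**What the plan says.** The Aim 1 section words its hypotheses as comparisons between conditions. For the single strategies: "We hypothesize that augmenting REP with TEAM alone or LEAD alone is superior to Standard REP". For the combination: "TEAM + LEAD is superior to all other conditions because it targets both levels". The sentence comes directly after the secondary clinical outcomes and is not limited to implementation outcomes.

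Under Statistical analyses, Aim 1, the primary tool for all these outcomes is "a two-way analysis of variance with interaction using mixed-effects linear models for continuous outcomes", with generalized linear mixed models for categorical variables. For patient outcomes the hypothesis is that "relative to REP only, TEAM, LEAD, and their interaction will significantly improve (1) child symptom severity and (2) quality of life". The implementation paragraph uses the same construction for encounters per case and competencies.

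The two paragraphs then differ. The implementation paragraph ends: "We will conduct planned contrasts to test differences between conditions". The patient paragraph says "Fixed effects include time and condition, and random effects will account for nesting", mentions exploratory adjusted models, and names no contrast. Neither paragraph gives the coding of condition.

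**The concern.** The two sections do not state the same hypotheses. Superiority of the combination is three pairwise statements: better than REP, than TEAM and than LEAD. An interaction is one statement: the combination does more, or less, than the sum of the two separate effects. The reason given in Aim 1, that the combination acts on both levels, needs no synergy; two effects that add would satisfy it. The analysis hypothesis would then fail although the Aim 1 hypothesis is true.

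The single-strategy terms raise a second question. In a conventional two-way ANOVA the TEAM main effect averages TEAM versus REP with TEAM + LEAD versus LEAD. That is a legitimate factorial estimand, but it is not an effect relative to REP alone.

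At stake is how the secondary clinical results are read: whether each strategy works alone, and whether adding the second improves on either one.

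**Working it through.** **Inputs.** From Setting and participants: 24 practices and up to 600 caregivers. From Power and sample size: six practices per condition, 20% attrition, ICC 0.01 (stated for cases of the same provider), and a detectable effect of 0.25 for patient outcomes. Hence 600 × 0.8 = 480 analysed, or 120 per condition and 20 per practice. My assumptions: two-sided alpha 0.05, SD 1, positive values meaning improvement, the effect patterns below, and a design effect (DE) between 1.00 and 1 + 19 × 0.01 = 1.19, the upper end applying the ICC at practice level.

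**The plan's own figure.** For an effect of 0.25 at 80% power (assumed), n per arm = 2 × (1.960 + 0.842)² / 0.25² = 251.2, or 252 with the t correction. With about five cases per provider (assumed), DE = 1.04 and 252 × 1.04 = 262.1. The stated 262 per condition therefore reproduces for a two-group comparison. It cannot describe the four cells, since 4 × 262 = 1,048 exceeds 600.

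**What each term tests.** Let R, T, L and B be the means under REP, TEAM, LEAD and both.
- Averaged TEAM main effect: [(T − R) + (B − L)] / 2
- Interaction: (B − L) − (T − R)
- TEAM alone versus REP: T − R
- Combination superior: B − R, B − T and B − L all positive

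**Standard errors** (DE 1.00; DE 1.19).
- Pairwise contrast: √(2·DE/120) = 0.129; 0.141
- Main effect: √(DE/120) = 0.091; 0.100
- Interaction: √(4·DE/120) = 0.183; 0.199

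The chance of a favourable significant result is Φ(effect/SE − 1.96).

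**Case A, additive: R, T, L, B = 0, 0.25, 0.25, 0.50.** The combination is best, as Aim 1 says.
- Interaction: (0.50 − 0.25) − (0.25 − 0) = 0, so 2.5% in the favourable direction, whatever the sample size
- Each main effect: 0.25/0.091 = 2.74, giving 78%; 71% at DE 1.19
- TEAM versus REP: 0.25/0.129 = 1.94, giving 49%; 43%
- Combination versus REP: 97%; 94%
- Combination better than all three (simulated cell means): 32%; 26%

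**Case B, only the combination works: 0, 0, 0, 0.50.** TEAM alone equals REP.
- Averaged TEAM main effect: (0 + 0.50)/2 = 0.25, significant in 78%; 71%
- TEAM versus REP: 2.5% in the favourable direction
- Interaction: 0.50/0.183 = 2.74, significant in 78%; 71%
- Main effect significant without a significant interaction (the two contrasts are orthogonal): 0.78 × 0.22 = 17%; 0.71 × 0.29 = 21%
- Combination better than all three: 93%; 87%

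If the combination effect is only 0.25, the main effect and the interaction are each significant in 28%; 24%.

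**Coding.** With REP as reference level, the TEAM and LEAD coefficients are T − R and L − R, which match Aim 1, and the false-positive rate in Case B returns to 2.5%. The interaction coefficient is still B − T − L + R, so Case A is unchanged.

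**The case against.** A reader might infer that patient outcomes will be tested only by main effects and the interaction. The text does not say so. Power and sample size describes "comparisons of provider and patient outcomes among the six practices in each of the four conditions in the factorial design", so comparisons between conditions on patient outcomes appear to be intended, and a condensed article may leave its list of contrasts to the analysis plan. That stands: a missing list alone would be no finding. What remains is a hypothesis that is written down, twice, and differs from the one in Aim 1.

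A reader might also infer that an ineffective single strategy will be declared effective. That needs averaged main effects. The wording about REP only, and the model term condition, also allow REP-reference coding, under which it does not follow. Even with averaged effects the interaction would usually give warning when synergy is strong (78 to 71% in Case B), though not when the combination effect is 0.25.

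Nor does it follow that a true combined advantage would go unreported. In Case A both main effects are significant together in 0.78² = 61% (0.71² = 50% at DE 1.19), more often than the three contrasts succeed. This is fair, but the inference from two main effects to a best combination assumes additivity. If benefits saturate (0, 0.25, 0.25, 0.25), the combination adds nothing, yet both main effects are significant in 0.277² = 8% (0.240² = 6%), against 0.4% for the three-contrast rule.

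Finally, the outcomes affected are secondary, and the primary outcome has planned contrasts. That limits the severity.

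**Conclusion.** The point holds in this form: the interaction named in the analysis hypotheses does not test superiority of the combination under any coding, and the single-strategy terms test the Aim 1 hypotheses only if REP is the reference level, which the text does not settle. Under additive effects the first mismatch means a favourable interaction in about 2.5% of trials in which the Aim 1 statement is true. That figure depends on neither sample size nor ICC. The other percentages rest on the assumed effect patterns, 120 analysed cases per condition and DE 1.00 to 1.19. I used 0.25 because the plan gives it for patient outcomes; its 0.42 belongs to the number of DOCC sessions and does not apply here.

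Severity is minor to moderate. The documents do not show that the wrong strategy would be recommended. They show a hypothesis and a test that need to be matched, most clearly for the secondary patient outcomes.

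**What to change.** In Statistical analyses, Aim 1:

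1. Extend the planned-contrast sentence to patient outcomes.
2. For both outcome types, tie the Aim 1 hypotheses to named contrasts: TEAM versus REP; LEAD versus REP; and TEAM + LEAD versus each of REP, TEAM and LEAD. Conclude that the combination is superior only if all three of its contrasts favour it. Because all must hold, that conclusion needs no alpha adjustment across the three.
3. State how condition is coded.
4. Keep the factorial main effects, described as average effects over the levels of the other strategy.
5. Describe the interaction, with its confidence interval, as the test of synergy only, and remove it from the claim of improvement relative to REP.

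The cost is analysis wording and a few contrast statements; data collection does not change. The downside is precision. At 0.25 per strategy with additive effects, TEAM versus REP has 49 to 43% power and the all-three rule 32 to 26%. With t tests on 20 practice-level degrees of freedom and ICC 0.01 these fall to about 39% and 24%. The contrasts should therefore be reported as estimates with confidence intervals, and a non-significant result should not be read as evidence that conditions are equal.
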